## Abstract

**Background:**

Chronic atrophic gastritis (CAG) is widely recognized as one of the precancerous lesions of gastric cancer. *Helicobacter pylori* is one of the important risk factors for CAG and gastric cancer. However, a large proportion of patients with CAG cannot avoid developing gastric cancer even after eradicating *H pylori*. It is necessary to find a safe and effective treatment to suppress this “inflammation-cancer” progression. The Qi-Lian-Xiao-Pi prescription (WW-1), a traditional Chinese medicine (TCM), has been reported to be effective in the treatment of CAG. However, the evidence is subject to methodological limitations.

**Objective:**

This study aimed to evaluate the efficacy, safety, and mechanism of the WW-1 in patients with CAG following successful *H pylori* eradication.

**Methods:**

This study is a rigorous parallel-arm, randomized, placebo-controlled, multicenter, double-blinded trial. A total of 110 eligible participants with a confirmed diagnosis of CAG after *H pylori* eradication are being enrolled and randomly assigned in a 1:1 ratio to either the intervention group (WW-1) or the control group (WW-1 placebo). Key eligibility criteria include confirmed CAG by histopathology, documented successful *H pylori* eradication, and compliance with predefined inclusion and exclusion criteria. The treatment duration is 24 weeks. Blinded histopathological assessments using the Operative Link on Gastritis Assessment and Operative Link on Gastric Intestinal Metaplasia Assessment staging systems will serve as primary outcomes. Secondary outcomes include improvement rates of gastric mucosal gland atrophy and intestinal metaplasia, as well as TCM syndrome scores. Safety will be assessed through monitoring vital signs, adverse events, blood, urine, and stool tests, liver and kidney function, and electrocardiography. Additionally, gastric mucosal DNA methylation and metagenomic sequencing of digestive tract microbiota (including saliva, tongue coating, gastric, and intestinal samples) will be analyzed to explore potential mechanisms of WW-1.

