### Sample Size Calculation

The superiority test of the outcome measure Operative Link on Gastritis Assessment (OLGA) improvement rate was used as a categorical variable, and the sample size of the control group was estimated by n1. n2 represents the sample size of the control group, k represents the ratio of the number of cases between the 2 groups (k=1), and the minimum clinically meaningful difference is set △=10%. According to the results of the team’s previous research, π1=45%, π2=10% [12]. By further incorporating a 2-sided significance level (α) of 0.05 and a statistical power of 80%, the calculation yielded n2=43 and n1=43. Considering the 20% clinical dropout rate, the sample size was determined to be 108 cases, that is, 54 cases in the experimental group and 54 cases in the control group.

For the superiority test of categorical variables with the improvement rate of the outcome measure Operative Link on Gastric Intestinal Metaplasia Assessment (OLGIM), in which △=10%, k=1, π1=42%, and π2=8% [12], using the same significance level (α=0.05) and statistical power (80%), the calculation yielded n2=44 and n1=44. Considering the 20% clinical dropout rate, the sample size was determined to be 110 cases, that is, 55 cases in the experimental group and 55 cases in the control group.

The larger calculated sample size was chosen to ensure adequate statistical power. Therefore, the sample size was 110 cases, 55 cases in the experimental group, and 55 cases in the control group.

[figure not shown]

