### Outcome Evaluation

The primary outcome, OLGA improvement, is evaluated based on assessments at baseline (visit 1) and posttreatment (visit 8). The severity of gastric atrophy is assessed at baseline and post-treatment according to the OLGA staging system, with the overall stage at each time point determined by the most severe atrophic grade across all biopsy sites. Patients are categorized into three groups based on changes in OLGA stage: regression, defined as a reduction of ≥1 stage after treatment; stable, defined as no change in OLGA stage after treatment; and progression, defined as an increase of ≥1 stage after treatment.

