Secondary outcomes include the improvement of gastric mucosal atrophy and IM (assessed at visits 1 and 8), as well as changes in TCM syndrome scores (assessed at visits 1, 2, 3, 4, 5, 6, 7, and 8). Based on the histopathological characteristics of CAG, a graded scoring system will be used for the pathological assessment. The severity of gastric mucosal atrophy and IM will be classified into 4 grades—absent, mild, moderate, and severe—which will be assigned scores of 0, 2, 4, and 6, respectively. In cases where multiple biopsy specimens or histological sections from a single patient exhibit varying degrees of lesions, the score corresponding to the most severe lesion will be assigned. The improvement in these pathological scores from baseline to posttreatment will be compared between the 2 groups. Additionally, clinical symptoms will be quantitatively evaluated using a standardized scoring method. The primary symptoms include stomach pain and fullness, while secondary symptoms encompass gastric discomfort, poor appetite, dry mouth, bitter taste in the mouth, belching, acid reflux, heartburn, and fatigue. The symptom grading criteria are formulated according to the *Guiding Principles for Clinical Research of New Traditional Chinese Medicines* (2002 edition). Specifically, primary symptoms will be comprehensively assessed based on their severity and frequency, and categorized into 4 grades (absent, mild, moderate, and severe), scoring 0, 2, 4, and 6 points, respectively. Secondary symptoms will be evaluated using the same 4-tier scale but will be scored as 0, 1, 2, and 3 points, respectively. The total symptom scores will be recorded at baseline and at 4-week intervals throughout the treatment period. Changes in the total symptom scores relative to baseline will be compared between the 2 groups to comprehensively assess symptom improvement.

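### The abstract makes OLGA and OLGIM the primary outcomes, the outcome section makes it OLGA alone, and OLGIM stage, which sets the sample size, is never ranked

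*Protocol article*

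**What the plan says.** The protocol article describes the primary outcome in three places.

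- **Abstract, Methods.** OLGA and OLGIM are paired, in the plural: "Operative Link on Gastric Intestinal Metaplasia Assessment staging systems will serve as primary outcomes".
- **Outcome Evaluation.** There is one, in the singular: "The primary outcome, OLGA improvement, is evaluated based on assessments at baseline (visit 1) and posttreatment (visit 8". Regression, stable and progression are defined for OLGA stage only. The next paragraph begins "Secondary outcomes include the improvement of gastric mucosal atrophy and IM (assessed at visits 1 and 8", and goes on to severity scores of 0, 2, 4 and 6 and to symptom scores. OLGIM stage is in neither list.
- **Sample Size Calculation.** Two separate calculations are given. OLGA uses "a 2-sided significance level (α) of 0.05 and a statistical power of 80" percent, with a margin: "the minimum clinically meaningful difference is set △=10" percent. OLGIM uses the same margin, "10%, k=1, π1=42%, and π2=8" percent, and "using the same significance level (α=0.05) and statistical power (80%), the calculation yielded n2=44 and n1=44". The larger total, 110 from OLGIM against 108 from OLGA, is adopted.

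The Statistical Analysis Plan section sets P≤.05, two-sided, for all tests and names a chi-square or Fisher exact test for qualitative data. It mentions no margin. Randomization is stratified by centre and by baseline OLGA/OLGIM stage.

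**The concern.** Which outcome is primary is core protocol content, and here two sections give different answers. The abstract and the paired sample-size calculations suggest two primary outcomes; the outcome section states one. An analysis plan could supply a testing order, but it could not follow both statements.

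The answer decides what the trial may claim. With two primaries, either-wins and both-required rules have different error rates and different power, and the article chooses neither. OLGIM is left in an odd position: it determines how many patients are enrolled, yet it has no rank and no responder definition in the outcome section.

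**Working it through.** **Inputs** (Sample Size Calculation): OLGA 45% vs 10%; OLGIM 42% vs 8%; margin 10 points; two-sided alpha 0.05; power 80%; dropout 20%. The article gives no correlation between the two endpoints, so all correlations (ρ) below are assumed.

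**1. Reproducing the stated N.** Superiority by a margin, unpooled variance:

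n = (1.960 + 0.842)² × [p1(1−p1) + p2(1−p2)] / (p1 − p2 − 0.10)²

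- OLGA: 7.849 × 0.3375 / 0.25² = 42.4, so 43 per arm; 43/0.8 gives 54; total 108.
- OLGIM: 7.849 × 0.3172 / 0.24² = 43.2, so 44 per arm; 44/0.8 gives 55; total 110.

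Both match the article exactly.

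**2. Single primary (OLGA), 44 evaluable per arm.** SE = √(0.3375/44) = 0.0876. Power = Φ(0.25/0.0876 − 1.960) = Φ(0.895) = 81.4%. Alpha is 5%. For OLGIM the same calculation gives Φ(0.867) = 80.7%.

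**3. Two primaries, either suffices, each at 0.05.** At ρ = 0 the familywise error is 1 − 0.95² = 9.75%. The correlated values come from the bivariate normal. The one-directional figure counts only false results favouring WW-1; at ρ = 0 it is 1 − 0.975² = 4.9%, against a nominal 2.5%.

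| Assumed ρ | Two-sided familywise error | False favourable result |
|---|---|---|
| 0 | 9.75% | 4.9% |
| 0.5 | 9.1% | 4.5% |
| 0.7 | 8.3% | 4.2% |

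If the test is against the margin, these rates apply where the true difference equals 10 points; with no true difference they are lower.

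**4. Two primaries, both required, 44 per arm, 10-point margin.** At ρ = 0, 0.814 × 0.807 = 65.7%. The bivariate normal gives 70.2% at 0.5, 74.2% at 0.8 and 76.2% at 0.9.

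**5. Both required, no margin (the test named in the analysis section).**

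- Unpooled variance: OLGA Φ(0.35/0.0876 − 1.960) = 97.9%; OLGIM Φ(0.34/0.0849 − 1.960) = 98.0%; the product at ρ = 0 is about 96%.
- Pooled variance under the null: about 96.9% each, product about 94%.

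Positive correlation raises both.

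**6. N for 80% joint power with the margin, ρ = 0.** Each endpoint needs √0.80 = 89.4% power (z = 1.25). For OLGIM, (1.960 + 1.25)² × 0.3172/0.24² = 56.7, so 57 per arm; 57/0.8 gives 72; total 144.

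**The case against.** The outcome section is the operative definition. It is singular and gives visits and response categories, while the abstract is a summary. Sizing for a second important endpoint and taking the larger N does not make that endpoint co-primary. This stands, and on that reading nothing is wrong with alpha or power. A reader might infer from the two calculations at 0.05 that the error rate or the power is wrong as planned. The article does not support that: it follows only if the abstract's two-primary reading governs, and then only under a particular success rule.

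The power loss under a both-required rule also depends on the margin. The analysis section names a test without one, and with that test the loss is small. In addition, the joint figures assume 44 evaluable per arm; with all 55 contributing complete data, joint power against the margin would be 78.9% at ρ = 0.

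The 8% to 10% error counts findings in both directions, and a result favouring placebo is not a success. The one-directional figures are about half as large, though still well above 2.5%.

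A reader might also infer that the sponsor is free to pick the reading after seeing the data. That cannot be shown. The trial is registered, and the registry entry, full protocol and any separate analysis plan are not at hand. The absence of a multiplicity rule from a journal article is not a fault in itself.

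None of this removes the conflict between the abstract and the outcome section, or gives OLGIM stage a rank.

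**Conclusion.** The point holds as an inconsistency in the primary outcome, with conditional consequences.

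- **OLGA alone primary:** alpha 5%, power 81.4% against the margin, N = 110 sufficient. No statistical fault.
- **Two primaries, either wins:** two-sided familywise error 8.3% to 9.75%, or 4.2% to 4.9% for a false favourable result, over assumed correlations of 0.7 down to 0.
- **Two primaries, both required:** joint power about 66% to 76% (assumed correlation 0 to 0.9, 44 evaluable per arm) against the 10-point margin; about 94% to 96% at zero correlation, and more with positive correlation, without it.

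The sample-size arithmetic is correct. The power figures rest on the article's own response rates. What needs correcting is that the article does not settle which of these cases applies.

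**What to change.** Before unblinding, name OLGA regression (a fall of at least one stage) as the single primary outcome in the abstract, outcome and sample-size sections. Define OLGIM regression in the outcome section and list it as a key secondary outcome, tested at two-sided 0.05 only if OLGA succeeds. Present the OLGIM calculation as support for that key secondary.

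This follows the existing outcome section, and the fixed order controls the error rate across the two tests. N stays at 110, since OLGA needs 108. The cost is a documented wording change while enrollment is under way, and no confirmatory OLGIM claim if OLGA fails.

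If true co-primaries are intended, state that both must be significant, say whether the 10-point margin applies to the tests, and restate joint power for the test actually used: about 66% to 76% with the margin at 44 evaluable per arm. Reaching 80% joint power with the margin, assuming independence, would take about 144 participants.

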**Results:**

The funding began in November 2023. The study was officially initiated on April 20, 2025, with the enrollment of the first participant. The final study results, including efficacy outcomes, safety profiles, and mechanistic insights, are expected to be released in October 2026 after comprehensive data analysis and verification.

**Conclusions:**

This study is designed to determine whether WW-1 can improve CAG by modulating gastric mucosal DNA methylation and the digestive tract microbiota. It represents a prospective clinical trial in TCM that aims to evaluate therapeutic effects on CAG through the regulation of microbiota homeostasis and epigenetic mechanisms. The findings of this study are expected to provide evidence regarding the efficacy and safety of WW-1 and contribute to the development of therapeutic strategies and future drug research for CAG.

**International Registered Report Identifier (IRRID):**

DERR1-10.2196/90965

## Introduction

Chronic atrophic gastritis (CAG) is a common disorder of the digestive system and is widely recognized as a precancerous lesion of gastric cancer (GC) [1]. According to the International Agency for Research on Cancer, in 2022, there were approximately 968,000 new cases of GC worldwide, with over 660,000 deaths, ranking fifth in both incidence and mortality [2]. More than 70% of these cases occur in Asia, with nearly half in Eastern Asia, particularly China. CAG represents a key stage in the progression toward GC, with a prevalence of approximately 25% reported in studies conducted between 2010 and 2020 [3]. Among patients with CAG, the annual risk of developing GC is estimated at 0.1%, with cumulative incidences of 0.6% and 0.8% over 5 and 10 years, respectively [4].

*Helicobacter pylori* infection is the primary cause of CAG, inducing chronic inflammation of the gastric mucosa that leads to glandular loss, mucosal atrophy, and thinning, often accompanied by intestinal and/or pseudopyloric metaplasia [5]. Although *H pylori* eradication reduces GC risk in some populations, evidence indicates that a considerable proportion of patients with CAG remain at risk of progression even after successful eradication [6]. Notably, a large-scale Japanese cohort study (n=148,489) demonstrated that patients with *H pylori*–associated gastritis or gastric ulcer had a 2.0- to 2.4-fold higher risk of GC than those with duodenal ulcer after successful eradication, highlighting that persistent gastric mucosal atrophy is the key determinant of residual cancer risk [7].

The Correa cascade describes the stepwise progression of gastric carcinogenesis from normal mucosa to superficial gastritis, atrophic gastritis, intestinal metaplasia (IM), dysplasia, and ultimately GC [8]. Gastric mucosal atrophy, IM, and dysplasia are well-established independent risk factors for GC and represent critical stages in the inflammation-to-cancer transition. Despite advances in surgery, chemotherapy, radiotherapy, immunotherapy, and targeted therapies, the overall 5-year survival rate for GC remains low, ranging from 20% to 30% [9]. Therefore, effective interventions targeting the early stages of this cascade, particularly CAG, are urgently needed to prevent disease progression.

Current clinical treatments for CAG include acid suppression, *H pylori* eradication, and mucosal protection. However, due to the complex pathophysiology of CAG, these therapies often provide only partial symptomatic relief and limited reversal of histopathological changes. In recent years, traditional Chinese medicine (TCM) has gained increasing attention as a complementary therapeutic approach. Several TCM formulas, such as Xiao-Jian-Zhong-Tang, Sha-Shen-Mai-Dong-Tang, and Jian-Pi-Yi-Qi-Tang, have demonstrated potential benefits in improving CAG in clinical studies [10]. Mechanistically, TCM formulas may modulate multiple pathways, including inflammatory responses, cell proliferation and apoptosis, mucosal metabolism, and tissue repair. Nevertheless, most existing studies are limited by small sample sizes, single-arm designs, or insufficient methodological rigor. High-quality multicenter, randomized, double-blind, placebo-controlled trials remain scarce, despite being the gold standard for evaluating clinical efficacy [11].

Qi-Lian-Xiao-Pi prescription (WW-1), a modified formula derived from Ban-Xia-Xie-Xin-Tang, is widely used in China for the treatment of CAG. This standardized TCM formulation consists of *Pinelliae Rhizoma Praeparatum Cum Alumine* (Qing Banxia), *Scutellariae Radix* (Huangqin), *Coptidis Rhizoma* (Huanglian), *Zingiberis Rhizoma* (Ganjiang), *Curcumae Radix* (Yujin), and *Astragali Radix* (Huangqi), among other components. The formulation is developed based on long-term clinical practice and the core pathogenesis theory of “deficiency, stagnation, depression, and blood stasis” in TCM. It aims to strengthen the spleen and replenish deficiency, regulate gastrointestinal function, soothe the liver and relieve depression, promote the flow of qi, and resolve blood stasis to prevent disease progression. A multicenter randomized controlled trial confirmed that WW-1 significantly reverses gastric atrophy and IM, particularly in high-risk gastric corpus and incisura angularis lesions, with a favorable safety profile [12]. Experimental studies suggest that WW-1 may exert anti-inflammatory effects by inhibiting a disintegrin and metalloproteinase 17 activity and reducing tumor necrosis factor-α secretion [13]. In vitro studies also indicate that WW-1–containing serum can suppress S100A9 expression in M2 tumor-associated macrophages, thereby inhibiting proliferation and migration of GC cells and promoting apoptosis. However, robust clinical evidence supporting its efficacy and underlying mechanisms in patients with CAG, particularly after *H pylori* eradication, remains insufficient.

In addition, the digestive tract microbiota, including the gut, gastric, oral, and tongue-coating microbiota, has emerged as an important factor in the pathogenesis and progression of CAG. The gut microbiota functions as a complex and dynamic system that contributes to host metabolism, immune regulation, and homeostasis. Microbial metabolites, such as short-chain fatty acids and bile acids, play key roles in host-microbiota interactions [14,15]. Increasing evidence suggests that TCM formulations may exert therapeutic effects by modulating microbiota composition and metabolic activity [16]. Moreover, microbiota from different regions of the digestive tract, including saliva, tongue coating, and gastric mucosa, may also be involved in CAG progression [17-20].

Therefore, this study aims to evaluate the efficacy and safety of WW-1 in patients with CAG following successful *H pylori* eradication through a multicenter, randomized, double-blind, placebo-controlled trial. In addition, this study seeks to investigate the potential mechanisms of WW-1 by analyzing gastric mucosal DNA methylation and the composition of digestive tract microbiota. We hypothesize that WW-1 can improve histopathological outcomes in CAG and exert therapeutic effects by modulating epigenetic regulation and microbiota homeostasis.

## Methods

### Study Design

This trial adopted a multicenter, randomized, double-blind, placebo-controlled design with balanced allocation (1:1) across 2 arms, enrolling a total of 110 participants (55 per study group). This protocol is version 02, dated March 25, 2023. The study is registered with the Chinese Clinical Trial Registry (ChiCTR2400084357) on May 15, 2024. This protocol is described according to the SPIRIT (Standard Protocol Items: Recommendations for Interventional Trials) 2013 and SPIRIT-TCM (Standard Protocol Items for Clinical Trials with Traditional Chinese Medicine: Recommendations, Explanation and Elaboration) 2018 [21].

### Recruitment

Recruitment is conducted through multiple channels, including public advertisements (posters, social media, and community outreach) and the identification of potential participants from gastroenterology outpatient and previous inpatient lists. Eligible patients are comprehensively informed about the study’s purpose, procedures, treatment duration, potential benefits, and risks. A gastroenterology specialist confirms the diagnosis for all patients who express interest. Written informed consent must be obtained from each participant prior to randomization. All patient information will be kept confidential. Patients may withdraw at any trial stage, and the reasons for patient withdrawal will be well documented. The flowchart of this trial is shown (Figure 1).

**Figure 1 figure1:**
[figure not shown]
Participant flowchart. WW-1: Qi-Lian-Xiao-Pi prescription.

Participant enrollment is conducted within a multicenter framework involving 4 tertiary hospitals, each with an established gastroenterology service and access to a defined patient population with CAG. Recruitment is carried out through parallel approaches, including outpatient screening, inpatient record review, and community-based outreach. Screening and enrollment procedures are standardized across centers, with unified protocols applied at each site. Recruitment progress is monitored throughout the study period in relation to the planned timeline. As of the time of manuscript submission, patient enrollment is ongoing. The first patient was enrolled on April 20, 2025, and the study is projected to conclude in October 2026.

### Participants Selection

#### Diagnostic Criteria

##### Endoscopic Observation Grading Standard

Endoscopic atrophy was graded as mild, moderate, or severe according to the following criteria: mild: red-white appearance, predominantly white, visible vascular network, often focal. Moderate: red-white appearance, predominantly white, clearly visible vascular network, often diffuse, mucosal folds flattened/shallow. Type B atrophy extends from the antrum to the gastric angle level. Severe: above features plus granular/nodular hyperplastic changes. Type B atrophy extends to the upper/middle gastric body.

